## **12.7 ASSESSMENT OF EFFICACY**

### **12.7.1 Subject Diary / Common cold assessment at V2**

In the daily subject diary, from V1 on, subjects will be asked to answer the questions "Do you think/feel you have a cold?" or "Do you think/feel you are coming down with a cold (might be having first signs of cold)?" (in the morning and in the evening).

From the first day they answer „Yes“ to either of the above questions, they will have to start filling out the cold diary instead, to:

- record their symptoms on the Jackson scale (twice daily, in the morning and in the evening)
- record their symptoms on the Sore Throat Scale (twice daily, in the morning and in the evening)
- record their symptoms on the Irritated Throat Scale (twice daily, in the morning and in the evening)
- fill out the Wisconsin Upper Respiratory Symptom Survey (WURSS-21) Quality of Life section (once daily, in the evening)
- answer the question "Do you think that you are still sick with this respiratory infection?" (once daily, in the evening)
- record the use of IP (verum group only; once daily, in the evening)
- record the use of any concomitant treatment / remedies (once daily, in the evening).

The cold diary should be filled out until 2 days after the subject is symptom free (=answering "No" to the question "Do you think that you are still sick with this respiratory infection?" for 2 days in a row).

The Jackson score (Jackson, 1958) is calculated by summing the following 8 symptom scores: sore throat, blocked nose, runny nose, cough and sneezing (local symptoms) as well as headache, malaise, and chilliness (systemic symptoms). Symptoms are assessed on a 4-point scale: 0 = none (symptom not present), 1 = mild (sensible, but not disturbing or irritating), 2 = moderate (symptoms sometimes disturbing/irritating), 3 = severe (symptoms disturbing/irritating most of the time).

The Sore Throat is a 0-10 Likert scale where 0=not sore and 10=very sore.

Irritated Throat Scale is a 0-10 Likert scale where 0=not irritated and 10=very irritated.

WURSS-21 (Barrett et al., 2009) is an evaluative illness-specific quality of life instrument with 21 items, designed to assess the negative impact of acute upper respiratory infection, presumed viral (the common cold). In this study, the QoL part of the WURSS-21 will be applied, from item 12 ("think clearly") to item 20 ("live your personal life").

**Wisconsin Upper Respiratory Symptom Survey – 21 --- Daily Symptom Report**

Day: \_\_\_\_\_ Date: \_\_\_\_\_ Time: \_\_\_\_\_ ID: \_\_\_\_\_

Please fill in one circle for each of the following items:

|                             | Not sick
0         | Very mildly
1      | Mildly
2           | Moderately
3       | Moderately
4       | Severely
5         | Severely
6         | Severely
7         |
|-----------------------------|-----------------------|-----------------------|-----------------------|-----------------------|-----------------------|-----------------------|-----------------------|-----------------------|
| How sick do you feel today? |  |  |  |  |  |  |  |  |

Please rate the average severity of your cold symptoms over the last 24 hours for each symptom:

|                  | Do not have this symptom
0 | Very mild
1        | Mild
2             | Mild
3             | Moderate
4         | Moderate
5         | Severe
6           | Severe
7           |
|------------------|-------------------------------|-----------------------|-----------------------|-----------------------|-----------------------|-----------------------|-----------------------|-----------------------|
| Runny nose       |          |  |  |  |  |  |  |  |
| Plugged nose     |          |  |  |  |  |  |  |  |
| Sneezing         |          |  |  |  |  |  |  |  |
| Sore throat      |          |  |  |  |  |  |  |  |
| Scratchy throat  |          |  |  |  |  |  |  |  |
| Cough            |          |  |  |  |  |  |  |  |
| Hoarseness       |          |  |  |  |  |  |  |  |
| Head congestion  |          |  |  |  |  |  |  |  |
| Chest congestion |          |  |  |  |  |  |  |  |
| Feeling tired    |          |  |  |  |  |  |  |  |

Over the last 24 hours, how much has your cold interfered with your ability to:

|                              | Not at all
0       | Very mildly
1      | Mildly
2           | Mildly
3           | Moderately
4       | Moderately
5       | Severely
6         | Severely
7         |
|------------------------------|-----------------------|-----------------------|-----------------------|-----------------------|-----------------------|-----------------------|-----------------------|-----------------------|
| Think clearly                |  |  |  |  |  |  |  |  |
| Sleep well                   |  |  |  |  |  |  |  |  |
| Breathe easily               |  |  |  |  |  |  |  |  |
| Walk, climb stairs, exercise |  |  |  |  |  |  |  |  |
| Accomplish daily activities  |  |  |  |  |  |  |  |  |
| Work outside the home        |  |  |  |  |  |  |  |  |
| Work inside the home         |  |  |  |  |  |  |  |  |
| Interact with others         |  |  |  |  |  |  |  |  |
| Live your personal life      |  |  |  |  |  |  |  |  |

Compared to yesterday, I feel that my cold is...

| Very much better      | Somewhat better       | A little better       | The same              | A little worse        | Somewhat worse        | Very much worse       |
|-----------------------|-----------------------|-----------------------|-----------------------|-----------------------|-----------------------|-----------------------|
|  |  |  |  |  |  |  |

WURSS-21® (Wisconsin Upper Respiratory Symptom Survey) 2004  
Created by Bruce Barrett MD PhD et al., UW Department of Family Medicine, [name]

The IP use should start when following conditions have been fulfilled:

- answering "Yes" to either of the questions in the subject diary: "Do you think/feel you have a cold?" or "Do you think/feel you are coming down with a cold (might be having first signs of cold)?"
- Jackson score of at least 1 (mild = sensible, but not disturbing or irritating) for any symptom except headache

Within maximally 3 days after start of the symptoms, the subject should attend the Visit 2 at the investigational site. If the limitation of 3 days may not be held due to e.g. weekend and/or holiday, the Visit 2 could take place on the day following the last non-working day but needs to be clearly documented in the CRF together with an explanation to the delayed visit. During Visit 2, the investigator will perform a physical examination and the study team (not the investigator) will check the subject diaries. The investigator will examine whether the symptoms reported by the subject are still present and if so, whether they are attributable to common cold or the subject suffers from another ailment (e.g. allergy, influenza, sinusitis, pharyngitis, tonsillitis, laryngitis, reflux disease, infectious mononucleosis etc.).

The IP should be used until 2 days after the subject is symptom free (=answering "No" to the question "Do you think that you are still sick with this respiratory infection?" for 2 days in a row), but not longer than 12 days in total.

A common cold episode is defined by the following criteria, which must be met by the subjects at least two days in a row:

- 1) answering "Yes" to the question "Do you think that you are still sick with this respiratory infection?" and
- 2) reporting at least 1 of 4 cold symptoms: nasal discharge (runny nose); nasal obstruction (plugged or congested); sneezing; or sore (scratchy) throat, and
- 3) scoring at least 2 points on the Jackson scale.

Based on the assessment of the symptoms recorded in the diary by means of the above criteria for a common cold episode, as well as the evaluation of any symptoms by the investigator at V2 (whether they are attributable to common cold), the percentage of subjects with prevention of common cold outburst (upon originally having experienced initial symptoms) will be assessed.

The duration of the cold symptoms is the number of days since start of cold symptoms until the end of the symptoms (defined as the last day with one or more symptoms followed by at least two symptom-free days (subjects have to answer "No" to the question "Do you think that you are still sick with this respiratory infection?" for 2 days in a row)).

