### 7.1 EFFICACY PARAMETERS

Main endpoints:

Evaluation of various assessments of common cold symptoms by the observed magnitude of treatment effects:

- Sore Throat Scale
- Irritated Throat Scale
- Jackson scale – total score, local symptoms, systemic symptoms, 2-item score (sore throat & malaise)
- WURSS-21 QoL subscore
- Percentage of subjects with prevention of cold outburst

Further endpoints [SEP]

- Duration of common cold symptoms
- Use of concomitant treatment / remedies
- Global evaluation of efficacy by subjects at study end

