### **10.5 METHODS OF RANDOMISATION AND BLINDING**

The clinical investigation will be conducted in a single-blind randomised manner. The subjects will be randomised at the screening visit. The randomisation list will be provided to the sponsor's assigned responsible person (not involved in the study) by the statistician responsible for generation of the randomisation list. The ratio of randomisation between the "IP group" (IP, and optional care as needed) and the "peer-group" (optional care only, no IP) will be 1:1. Random numbers will be assigned to the subjects in a sequential order based on time of random-

isation at each investigational site (several whole blocks will be allocated to each centre). Randomisation list will be concealed to the investigational sites. It will be stored under lock and key by the sponsor until database closure. After database closure and sign-off of the statistical analysis plan, the sponsor's responsible person will provide the randomisation list to the project manager at the CRO and the statistician responsible for the statistical analysis. The study allows for stratification with respect to centres (sites).

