## **10.6 BLINDING**

In this single-blind study, the subjects, the study site staff handling the IP and the study monitors will not be blinded to treatment assignment. The investigator performing the cold symptom assessment at V2, the project manager, the statistician and all further study team members will be blinded to treatment assignment.

The unblinded site study staff and the monitor(s) will take utmost care not to unblind the investigator performing the cold symptom assessment at V2 or any further blinded study team members at any occasion during the entire study duration.

The subjects will be instructed not to unblind the investigator.

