### 14.1.3 Statistical methods

All end points as well as the concurrent and safety variables will receive an explorative examination and will be descriptively assessed. For the metric data (continuous data) the statistical characteristics will be given (number, mean, standard deviation, median, extremes, quartiles). For ordinal data (discrete data) number, median, interquartile range and extremes will be calculated. If found suitable, ordinal data will be considered as supplementary metric data. For all nominal data the frequency distribution will be presented in frequency tables. The values of metric data can be merged in ordinal classes according to clinical criteria to determine their frequency distribution. Explorative estimation for the structural consistency of the groups regarded will be proved by a descriptive comparison of demographic data, values at screening and secondary (further) endpoints.

In case of generated statistical hypotheses from the above defined descriptive analyses, the subsequent exploratory statistical tests are as follows (for reasons of small samples and/or potentially non-normal distributions):

- Mann-Whitney-U test for comparison independent groups,
- Paired Wilcoxon test for the pre-post comparison within groups,
- Chi-Square test for the comparison of frequencies for independent groups.

All p-values from statistical tests are to be understood as exploratively. That means, the results may deliver interesting insights in the underlying object of research, but those findings don't qualify for a confirmative generalization. Because of the exploratory character of the study no adjustment for multiple testing will be accomplished.

The FAS population will consist of all randomized subjects for which at least one data point after onset of cold symptoms is available, and, for verum group only, who received at least one dose of IP upon onset of cold symptoms. The VCAS population will consist of subjects from FAS without any major violations of the CIP. The assignment to the study populations will be performed before unblinding and start of analysis.

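### The main endpoint on prevention of a cold counts only subjects who declare first symptoms knowing their arm, so more trivial declarations on verum than in control would look like prevention

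*Protocol*

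**What the plan says.** Protocol 7.1 lists "Percentage of subjects with prevention of cold outburst" among the main endpoints, which are judged by the observed size of the treatment effect. Section 12.7.1 defines it: from the diary criteria and the investigator's evaluation at V2, "the percentage of subjects with prevention of common cold outburst (upon originally having experienced initial symptoms) will be assessed".

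On timing and blinding, 10.5 states "The subjects will be randomised at the screening visit", 12.1 has verum subjects receive the spray at that same visit, and 10.6 states that "the subjects, the study site staff handling the IP and the study monitors will not be blinded to treatment assignment". The investigator who assesses symptoms at V2 is blinded.

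Onset is self-reported (10.2, 12.7.1). It needs a yes to having a cold or to possibly getting one, plus a "Jackson score of at least 1 (mild = sensible, but not disturbing or irritating) for any symptom except headache". A cold episode needs three criteria: still feeling sick, at least one of four named symptoms, and at least 2 Jackson points, "which must be met by the subjects at least two days in a row".

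Section 14.1.3 limits the FAS to subjects with data after onset and, in verum only, at least one dose. It checks the consistency of the groups by "a descriptive comparison of demographic data, values at screening and secondary (further) endpoints".

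**The concern.** Randomisation makes the arms comparable at V1. The prevention percentage is not computed on that population but on a subset that subjects select themselves into, up to 16 weeks later, knowing their arm. The entry bar (one mild symptom, once) is lower than the episode bar (2 Jackson points and the other criteria on two consecutive days). Anyone who clears the first and not the second adds one to both numerator and denominator, as a success.

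The product is described as intended for early use (sections 4 and 5), and in verum the declaration is what starts its use. A lower threshold for declaring onset in that arm is therefore plausible. If it occurs, a main endpoint shows prevention without any effect, and since the study exists to choose assessments by effect size, the endpoint could be chosen because of its artefact.

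The consistency check in 14.1.3 would not settle the matter. It includes the further endpoints, which 7.1 lists as duration of symptoms, remedy use and global evaluation of efficacy. These are post-randomisation outcomes and cannot show that the groups were comparable.

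**Working it through.** The protocol gives no event rate, alpha, power or calculated sample size for this endpoint, so there is no stated figure to reproduce.

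**Inputs from the protocol.** 300 expected randomised, 1:1 (9.1, 10.5): 300/2 = 150 per arm. Expected to reach the treatment phase: 200/300 = 66.7%. Frequencies are compared by an exploratory chi-square test (14.1.3).

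**Assumptions, not in the protocol.** No product effect; true onset in 60% (150 × 0.60 = 90 per arm); 20% of true onsets abort unaided (90 × 0.20 = 18); a share x of verum subjects, all without a true cold, declare an extra trivial onset; none of these progresses; controls add none; two-sided 0.05.

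**False difference.** Control: 18/90 = 20.0%. Verum: (18 + 150x)/(90 + 150x).

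| x | Verum | Difference | Rejection, uncorrected chi-square (simulated) |
|---|---|---|---|
| 5% | 25.5/97.5 = 26.2% | 6.2 points | about 17% |
| 10% | 33/105 = 31.4% | 11.4 points | about 44% |
| 15% | 40.5/112.5 = 36.0% | 16.0 points | about 72% |

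With a continuity correction the rejection rates are about 12, 37 and 66%. A single example with 23 extra onsets: 18/90 = 20.0% against 41/113 = 36.3%, uncorrected p = 0.011.

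**Sensitivity at x = 15%.**

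| Change | Control | Verum | Difference | Rejection |
|---|---|---|---|---|
| 30% of true onsets abort | 27/90 = 30.0% | 49.5/112.5 = 44.0% | 14.0 | about 54% |
| 30% of trivial onsets progress | 20.0% | (18 + 0.7 × 22.5)/112.5 = 30.0% | 10.0 | about 37% |
| Controls over-declare by 5% | 25.5/97.5 = 26.2% | 36.0% | 9.8 | about 33% |
| Controls over-declare by 10% | 33/105 = 31.4% | 36.0% | 4.6 | about 11% |

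**With the protocol's own onset fraction** (100 per arm, 20% aborting, 20 extra verum onsets): (20 + 20)/(100 + 20) = 33.3% against 20.0%, a difference of 13.3 points with about 0.60 chance of p < 0.05. If both arms add 20, both stand at 33.3% and there is no difference. The artefact needs differential declaration.

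**All randomised subjects as denominator.** If trivial onsets fall only on subjects who would never have a true cold, episodes are 0.60 × 0.80 = 48% in both arms. But V3, 16 ± 4 days after onset, is the final visit (Synopsis, 12.3), so a true cold after a trivial onset is not recorded. If trivial onsets are independent of true colds and come first half the time, verum shows 48% × (1 − x/2) = 46.8, 45.6 and 44.4% for x = 5, 10 and 15%. If they always come first, x = 15% gives 48% × 0.85 = 40.8%. The no-effect gap is then 48 − 44.4 = 3.6 points, or 7.2 at worst.

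In that same half-the-time case at 15%, declared onsets are 1 − 0.85 × 0.40 = 66%; trivial ones come first in 0.15 × (0.40 + 0.30) = 10.5%, true ones in 55.5%. The onset-conditional figure is (10.5 + 0.20 × 55.5)/66 = 32.7%, a false 12.7 points. The all-randomised rate reduces the bias without removing it.

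**The case against.** **The endpoint has a blinded component.** True: the V2 evaluation is part of the definition, so a reader should not infer that the consistency check in 14.1.3 is the only safeguard. But V2 asks whether symptoms are still present and, if so, whether a cold explains them. An onset already resolved by V2 is not filtered out; it supports the count as prevented.

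**One-sided over-declaration is conjecture.** This stands. A reader might infer that controls gain nothing by declaring onset. Section 11 does not support that: optional care is allowed during the cold period in both arms. Verum subjects also take on repeated daily applications, and both arms answer the same question twice a day. The protocol does not show that verum subjects will over-declare, and excess declarations among controls would bias against the product.

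**The 72% is an upper-end scenario.** Also right, as the sensitivity table shows. In addition, 14.1.3 makes the chi-square test conditional on hypotheses arising from the descriptive analysis.

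**The study is an exploratory pilot, and an SAP may add analyses.** Section 14.1.2 disclaims confirmatory generalisation. That limits what may be claimed but does not remove bias from a main endpoint judged by its magnitude. Nor is this a detail left open: the protocol itself fixes the onset-conditional denominator.

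**Conclusion.** The concern holds in conditional form. The denominator is self-selected after randomisation by subjects who know their arm, and entry to it is easier than meeting the episode definition. Under no effect, excess trivial declarations in verum of 5 to 15% give about 6 to 16 false points and rejection in about 17 to 72% of trials, on the assumptions listed. At 15% excess, the alternatives examined give rejection of 54% down to 11%. The true size of any differential declaration is unknown.

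Two stronger readings are not supported. One is that a spurious effect will occur; the documents show only that the design allows it. The other is that a rate per randomised subject would be equal in both arms and could decide whether prevention is real. Follow-up ends after the first declared onset and the episode criteria remain unblinded self-ratings, so that rate can also favour an inert product, by 3.6 to 7.2 points at 15% excess. Trivial onsets could also affect the symptom scores compared within the FAS, but that was not quantified.

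**What to change.** Keep the onset-conditional percentage and report beside it:

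- (a) the number and percentage of all randomised subjects who declare onset, by arm;
- (b) as a supportive analysis, the rate of criteria-defined episodes among all randomised subjects by time from V1, censoring subjects withdrawn once the treated number is reached (12.10.1).

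State that (b) reduces the bias without removing it, because a trivial onset can hide a later cold and the episode criteria are self-rated without blinding. Do not describe an onset-conditional difference as prevention when onset declaration differs between arms, and do not use (b) as an unbiased arbiter.

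In 14.1.3, restrict the consistency comparison to demographic and V1 screening data within the FAS, leaving out the further endpoints.

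Cost: one added analysis, largely on data already collected, since the diary runs from V1 and symptom-free subjects return it at the termination visit. The all-randomised estimate is diluted by subjects without onset, and episode data will be incomplete for those who do not continue at V2 (9.3).

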### **12.7.2 Global Evaluation of the Efficacy by the Subjects**

The subjects in the verum group will evaluate the efficacy of the IP (global scaled evaluation with "very good", "good", "moderate" and "poor") at study end.

## **12.8 ASSESSMENT OF SAFETY**

### **12.8.1 Blood Pressure and Pulse Rate**

Sitting blood pressure and pulse rate will be measured using standard products and procedures at all study visits.

### **12.8.2 Adverse Events**

Any AE that occurs during the course of the clinical investigation (for evaluation and reporting see section 13), will be recorded in the CRF.

### **12.8.3 Global Evaluation of Safety by the Subjects**

The subjects in the verum group will evaluate independently the safety of the investigational product by means of a global scaled evaluation with “very good”, “good”, “moderate” and “poor”.

## **12.9 ASSESSMENT OF FURTHER PARAMETERS**

### **12.9.1 IP usage**

Evaluation of IP usage (verum group) will be performed during statistical evaluation at study end, based on the return and documentation of unused investigational product (per vial weight for spray and item counting for capsules) as compared to study duration.

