## 5 DESCRIPTION OF THE INVESTIGATIONAL PRODUCT

CMS016317 is ColdZyme® Mouth Spray, a medical device classified as a Class I device (CE-marked and marketed since 2013) under Council Directive 93/42/EEC on Medical Device and MED-DEV Guidance Document 2.4/1. Rev 8, June 2010, with the following composition: glycerol, water, cod trypsin, ethanol (<1 %), calcium chloride, trometamol and menthol. The manufacturer of ColdZyme® Mouth Spray is Enzymatica AB, the study sponsor.

ColdZyme® Mouth Spray is to be used when exposed to cold viruses or early on when cold symptoms occur. It targets the mouth and throat, where cold viruses take hold and multiply.

The intended use of ColdZyme® Mouth Spray (according to the Instruction for Use, 2016):

- It reduces the probability of catching a cold
- it can help shorten the duration of a cold if used at an early stage of the infection.

In a recent non-clinical study (Stefansson et al, 2017), it was demonstrated that ColdZyme® Mouth Spray has a virus deactivating ability against four major common cold viruses. A virucidal efficacy suspension test was conducted using ColdZyme® Mouth Spray against each of the challenge viruses in suspension. ColdZyme® Mouth Spray deactivated rhinovirus type 1A by 91.7% (1.08 log10), rhinovirus type 42 by 92.8% (1.14 log10), human influenza A virus H3N2 by 96.9% (1.51 log10), respiratory syncytial virus (RSV) by 99.9% (2.94 log10) and adenovirus type 2 by 64.5% (0.45 log10).

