### 7.3 FURTHER PARAMETERS

- Assessment of IP usage (based on IP account) in verum group

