### 10.2 DOSAGE AND USE OF IP

The spray should be applied every second hour up to 6 times with each time 2 puffs (1 dose) per occasion. At V1, the subject will be instructed on the use and the application demonstrated.

[figure not shown]

Figure 2: Application of spray

Depending on the timepoint of treatment onset, there may be less IP applied on the first day of use.

The IP use should start when following conditions have been fulfilled:

- answering "Yes" to either of the questions in the subject diary: "Do you think/feel you have a cold?" or "Do you think/feel you are coming down with a cold (might be having first signs of cold)?"
- Jackson score of at least 1 (mild = sensible, but not disturbing or irritating) for any symptom except headache

The IP should be used until 2 days after the subject is symptom free (=answering "No" to the question "Do you think that you are still sick with this respiratory infection?" for 2 days in a row), but not longer than 12 days in total.

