## **12 CONDUCT OF THE CLINICAL INVESTIGATION**

### **12.1 VISIT 1 (V1, SCREENING, RANDOMISATION)**

- Oral and written information about the nature, purpose, possible risks and benefits of the study provided to the subjects by the investigator
- Written consent of the subject to participate; the subject understands the requirements of the clinical investigation and is willing to comply
- Questioning and documentation of the medical history, concurrent diseases and treatment, demographic and anthropometric data, and physical examination by the investigator
- Verification that the inclusion criteria are met and that there are no violations of the exclusion criteria
- Measurement of blood pressure and pulse rate
- Urinalysis and pregnancy test (for women with childbearing potential)
- Issue of subject diary and instruction for recording
- Randomisation
- Issue of IP (verum group) and instruction for use
- Questioning and documentation of possible occurrence of adverse events (AEs)

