## **12.4 TERMINATION VISIT (TV) FOR SUBJECTS WITH NO SYMPTOMS DURING THE STUDY PERIOD, 16 WEEKS +/-7 DAYS AFTER V1**

- Questioning and documentation of possible occurrence of AEs
- Questioning and documentation of new or changed concurrent treatment
- Return of the subject diary
- Return of IP (verum group)

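### IP usage is taken from total vial weight against study duration, which neither isolates use during the cold nor matches the treatment days

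*Protocol*

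**What the plan says.** Section 7.3 (and the synopsis) lists the parameter as "Assessment of IP usage (based on IP account) in verum group". Section 12.9.1 says how it is obtained: "based on the return and documentation of unused investigational product", measured "per vial weight for spray and item counting for capsules) as compared to study duration".

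Section 12.1 places "Issue of IP (verum group) and instruction for use" at V1, before any symptom. Section 8.2 allows up to 16 weeks per subject. Section 10.2 ties the start of use to onset: "The IP use should start when following conditions have been fulfilled", followed by a Yes to one of the two cold questions and a Jackson item score of at least 1 other than headache. Use ends 2 days after the subject is symptom free and may last no more than 12 days.

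Under section 12.7.1 the diary before onset holds only the two cold questions. From the first Yes the cold diary replaces it, and there verum subjects "record the use of IP (verum group only; once daily, in the evening".

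At V3 (section 12.3) both return and accountability of the IP are listed. At the termination visit (section 12.4) the only IP item is "Return of IP (verum group", and the footnote to the flow chart (section 21.2) agrees. Section 10.4, however, requires vial-weight accountability of used IP in general, without limiting it to V3.

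**The concern.** One weight difference from V1 to return adds together everything that left the bottle. If a verum subject sprayed before the onset conditions were met, those doses would enter the usage figure as use during the cold. Early use is conceivable: section 5 describes a product that "is to be used when exposed to cold viruses or early on when cold symptoms occur", and its stated intended use includes lowering the chance of catching a cold.

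The denominator is a second and independent problem. Treatment lasts at most 12 days, whereas study duration runs to V3 or to 16 weeks. A ratio of doses to study duration therefore does not measure adherence, whether or not anyone sprays early.

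At stake is whether the reported usage describes how the spray was used in the colds being analysed. A reader of the results would rely on that to judge whether a small observed effect reflects the product or poor use of it.

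**Working it through.** The protocol states no usage figure, power or sample-size calculation, so there is nothing to reproduce. The checks below apply its own rules.

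**Inputs from the protocol.** Up to 6 doses a day (synopsis, section 10.2); at most 12 treatment days (10.2); V3 at 16 ± 4 days (12.3); at most 16 weeks = 112 days (8.2); 300 expected randomised, 200 expected with onset (9.1); 1:1 allocation (10.5). I take 6 doses on every day; the first day may in fact have fewer.

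**1. Effect of the denominator.** A full course is 6 × 12 = 72 doses. Reading = 72 / (6 × days counted):

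| Days counted | Intended doses | Reading for a full 12-day course |
|---|---|---|
| 12 (treatment days) | 72 | 100% |
| 16 (nominal V3) | 96 | 75.0% |
| 20 (latest V3) | 120 | 60.0% |
| 112 (16 weeks) | 672 | 10.7% |

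A fully adherent subject whose use properly ends after 7 days takes 42 doses and reads 42/96 = 43.8% over 16 days. On this measure, equally adherent subjects score lower the shorter their cold.

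**2. Effect of doses before onset.** Even with the correct denominator, vial weight gives

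reading = (doses during the cold + doses before onset) / (6 × treatment days).

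For a subject who truly took 50% of the intended doses, with assumed numbers of earlier doses:

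| Treatment days | 0 earlier | 6 earlier | 12 earlier | 24 earlier |
|---|---|---|---|---|
| 5 (15 of 30) | 50.0% | 70.0% | 90.0% | 130.0% |
| 7 (21 of 42) | 50.0% | 64.3% | 78.6% | 107.1% |
| 12 (36 of 72) | 50.0% | 58.3% | 66.7% | 83.3% |

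Diary doses from onset would read 50% in every cell, provided the diary is accurate.

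**3. What the two errors do together.** Early doses push the reading up, and a study-duration denominator pushes it down. The direction of the net error for a given subject cannot be stated.

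**4. What existing data could show.** Weight-derived doses minus diary doses estimate unrecorded use. The estimate is crude: the protocol gives no weight per puff, and any under-recording in the diary looks the same as early use. It also gives no timing.

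Onset can be compared by arm over all randomised subjects, but weakly. With 150 per arm, 100 onsets expected in each, and two-sided alpha 0.05 (assumed), suppose a share f of verum subjects spray early with relative risk reduction r (both assumed). Verum onsets = 100 × (1 − f × r):

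- f = 0.1, r = 0.3: 97 onsets, power about 6%
- f = 0.3, r = 0.3: 91 onsets, power about 19%
- f = 0.5, r = 0.5: 75 onsets, power about 84%

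Modest early use would probably go unnoticed in that comparison.

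**The case against.** The strongest reply is that the needed data are largely collected already. The cold diary records IP use daily from the first Yes, so use during the cold is captured directly. Section 10.4 requires weighing without restricting it to V3, and the visit list in section 12.4 does not forbid it. In a subject who never had symptoms, any weight lost from the bottle would point to early use. Onset can be compared between randomised arms. A statistical analysis plan not shown here could combine these sources. All of this stands.

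A reader might therefore infer too much: that early spraying cannot be detected, that the usage figure is inflated, or that the treatment comparison mixes a preventive with a treatment effect. The documents support none of these. Spraying before onset would breach section 10.2, subjects are instructed at V1, and nothing shows that it happens or how often. Its frequency and any effect on onset are assumptions.

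It is also fair that usage is only a further parameter in an exploratory pilot, and that the full analysis set requires a single dose upon onset (section 14.1.3).

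What the reply does not remove is that sections 7.3 and 12.9.1 name the IP account as the source and study duration as the comparator. The diary record feeds no listed usage parameter. An analysis plan can change the definition, but it cannot recover the timing of early use that no form requests.

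**Conclusion.** The point holds as a minor defect in how one parameter is defined. The stated measure cannot separate doses before onset from doses during the cold, and its comparator does not match the treatment days. The denominator problem is certain on the text: a full course reads between 100% and 10.7% depending only on the days counted. The contamination by early doses is conditional. If it occurs, 6 to 12 such doses would lift a true 50% in a 7-day cold to between 64.3% and 78.6% against the correct denominator.

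These figures assume 6 doses on every treatment day, and the counts of earlier doses are illustrative. Early use is not shown to occur. It could be estimated crudely from weight minus diary doses, but its timing and any link to onset would not be recorded. No conclusion about bias in the efficacy comparison follows.

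**What to change.** - In sections 7.3 and 12.9.1 and the synopsis, define IP usage as diary-recorded doses from onset to IP stop, divided by the doses intended under section 10.2 over those treatment days. Keep vial weight as a cross-check, with weight-derived doses minus diary doses reported as unrecorded use.
- List vial weighing at the termination visit in sections 12.4 and 21.2, so that they agree with section 10.4.
- Remove or reconcile the reference to capsules in section 12.9.1; the only IP described is a spray.
- Have unblinded staff ask verum subjects once about any use before onset: at V2 for those with onset, at the termination visit for those without. Someone other than the investigator already reviews the diary at V2, so the blind assessment is not affected. A daily verum-only diary line is less suitable because it could itself prompt early spraying.
- Report onset by arm over all randomised subjects, alongside any reported early use.

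**Cost.** One question, one extra table, and about 50 weighings of bottles that are returned anyway: 300/2 = 150 verum subjects, of whom 150 × 200/300 = 100 are expected to have onset, if onset is equally frequent in both arms. The usage figure would then rest on self-reported diary doses, and a single retrospective question is open to recall error.
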